### 2.4. Biological Sample Collection

#### 2.4.1. Collection of Peripheral Venous Blood Samples

Peripheral venous blood samples will be taken during a regular visit to OI Ljubljana up to 4 weeks before the start of treatment, the 12th (+/−2) and the 28th (+/−2) week, in the event of suspected disease progression/hyperprogression and in the event of the occurrence of immunologically unwanted side effects (colitis or other immune-related side effects).

During regular blood sampling, a sample of blood will be taken from the examinee for additional tests—a total of 10 mL, of which 5 mL will be used for cytologic tests (specific immune host cell concentration) and another 5 mL of the venous blood will be used for molecular tests (messenger RNA for PD-L1 and IFNγ expression).

#### 2.4.2. Collection of Tumour Samples

Histological material from the tumor tissue will be obtained before the start of immunotherapy treatment. At the Department of Pathology of the Ljubljana Oncology Institute, multitumor blocks and cut material for molecular examinations will be prepared from histological samples.

#### 2.4.3. Collection of Stool Sample

The patient will submit a stool sample during regular defecation, before the start of treatment, at the 12th (+/−2) and 28th (+/−2) week, in the event of suspected disease progression/hyperprogression and in the event of the occurrence of immune adverse side effects (colitis or other irAE). According to the received instructions, they will send it by post in the attached envelope together with the completed questionnaire. In the case of antibiotic treatment, the collection of the stool sample will be postponed and taken 3 weeks after the antibiotic treatment has been completed. The samples stored in the OMNIgene transport medium will be sent to the Faculty of Biotechnology of the University of Ljubljana, where microbiome analysis will take place.

### 2.5. Sample Analysis

#### 2.5.1. Gut Microbiome, Metagenome and Virome Analysis

The samples stored in the OMNIgene transport medium will be sent to the Faculty of Biotechnology of the University of Ljubljana, where the microbiome analysis will take place. After the successful isolation of total microbial DNA from thawed stool samples using the appropriate protocols (with a special procedure that will include the removal of non-viral particles by centrifugation and filtration through membrane filters with 0.2 μm pores), we will also obtain viral DNA from a smaller, selected set of samples, to approach the analysis of the microbiome, metagenome and virome. We will analyze the structure and changes in the intestinal microbiome with the so-called by amplicon sequencing of 16S rRNA—we will use the technology Illumina 16S/ITS Nextera two-step PCR &MiSeq 2 × 300. The variable regions of genes for 16S rRNA will be analyzed with appropriate bioinformatic and biostatistical analysis: UPARSE pipeline, qualitative filtering with parameter settings that will be optimized after analyzing the so-called “mock” pattern. The identification of operational taxonomic units (OTE) with the “usearch global” function in Silva NR SSU and LTP SSU databases, taxonomic classification in OTE with Wang’s method built into the software package Mothur v 1.35. Taxonomy, OTE tables and phylogenetic trees will be made with the “R” package phyloseq for statistical analysis and graphics.

We will perform metagenomic sequencing by constructing appropriate Nextera libraries and sequencing with the Illumina NovaSeq6000 2 × 150 bp platform. We expect 20 million readings per sample. We will process the acquired sequences accordingly (quality filtering with FastQC, Trimmomatric), remove human sequences with bbmap, and analyze the sequences with established metagenomic software packages (pipelines, e.g., Assnake). We will obtain taxonomic and functional profiles of processed metagenomes with MeatPhIAn3 and HUMAnN2 tools and the KEGG database.

Analysis of virome composition will be performed by metagenomic sequencing, for which we will use Illumina NovaSeq technology, TruSeqlibrary, 2 × 150 bp, and we will obtain up to 5 mio. of readings per sample. We will process the acquired sequences accordingly (quality filtering with FASTQC, Trimmomatic) and assemble contigs (with the metaSpades assembler). We will keep only those that we will recognize with the appropriate tools (Virsorter) or will be recognized in the RefSeq Virus database with Blast, and we will remove all bacterial chromosomal DNA contigs.

#### 2.5.2. Tumor Tissue and Peripheral Blood Analysis

The MagMAX™ FFPE DNA/RNA Ultra Kit will be used to isolate RNA from paraffin. Tissue slices (40 µm) will be prepared from the tumor blocks in the Department of Pathology, after which further analysis will take place in the Department of Experimental Oncology. Initially, the paraffin will be dissolved with the addition of xylene, by centrifugation and heating the samples to 50 °C. This will be followed by rinsing with 100% ethanol and drying the sample with a fixed tissue. The tissue sample will be incubated with protease buffer for 1 h at 50 °C and 1 h at 90 °C. RNA buffer will be added to bind the RNA to the magnetic beads. To remove DNA, a DNAse solution will be added after washing. This will be followed by repeated washing and centrifugation with the elution solution until the RNA supernatant is obtained. The sample will be stored at −80 °C until analysis. Sample analysis will be performed by RT-qPCR.The Plasma/Serum Circulating and Exosomal RNA Purification Kit (Slurry Format (Norgen Biotek Corp., Ontario, Canada)) will be used to isolate RNA from plasma. The analysis will take place on 5 mL of venous blood samples. Blood plasma will be prepared from them by centrifugation. To bind the RNA to the pellets, a 2 mL plasma sample will be incubated with lysis buffer at 60 °C. Then, after adding 100% ethanol, it will be centrifuged. For greater purity, the process will be repeated twice. The ultracentrifugation process will bind the mixture to the column. This will be followed by washing the sample and adding DNase to remove the DNA. The sample will be processed twice more by washing and ultracentrifugation to obtain the supernatant with RNA, which will be stored at −80 °C. RNA concentration will be determined spectrophotometrically with a Qubit fluorometer (Applied Biosystems, Massachusetts, USA). Analysis of the samples is expected to be done by ddPCR.PD-L1 expression on CD4+, CD8+ T lymphocytes and macrophages will be determined using the flow cytometric method. Antibody panels for 7-color flow cytometric measurements (antibodies from BD Biosciences (San Jose, CA, USA), BioLegend (San Diego, CA, USA) and Beckma Coulter (Brea, CA, USA)) will be used. Samples will be measured using a FACSCanto 10 flow cytometer (BD Biosciences). FACSDiva software (BD Biosciences) will be used to analyze flow cytometry results.Serum interferon gamma concentration: Quantikine human IFNγ ELISA kit (R&D Systems™, Minneapolis, USA) will be used to determine serum interferon gamma concentration.For the qRT-PCR assay, SYBR Green chemistry will be used, which enables relative, as well as absolute, quantification of the target sequence in the investigated sample. Relative quantification will be used to determine the expression level of the transgene in the paraffin samples. Additionally, absolute quantification will be used to determine the target sequences in the plasma of the patients using ddPCR. For both relative and absolute quantification, we will use specific set of primers (PrimeTime qPCR Primers, IDT Technologies, Coralville, IA, USA) that do not amplify any other known dsDNA sequence, and are specific for the IFNγ sequence and CD274 (PD-L1) sequence (primer details are in Table 2).Sample preparation for flow-cytometric measurement will be carried out as previously described by our group [38,39]. Used antibodies (Table 3) will be divided into 2 separate tubes according to the analyzed immune cells, and half a million cells per 100 μL will be used for each tube. Immune cells will be gated according to their immunophenotype: T cells (CD3+); the helper T cell subset (CD4+); cytotoxic T cell subset (CD8+); and macrophages (CD11b+CD14+), as well as their M1-like (CD86+) and M2-like (CD206+) subsets. Percentages of T cells and macrophages will be calculated as a ratio per CD45+. Percentages of CD4+ and CD8+ T cell subsets will be given as a percentage of CD3+, while M1-like and M2-like macrophage subsets will be given as a percentage per all macrophages. The expression of PD-1 and PD-L1 will be analyzed on both T cells and macrophages, as well as on their corresponding subsets. The correlation of the analyzed immune cells and their subsets with patient PFS and OS will be also calculated. Survival analysis will be based on an X-year patient follow-up. Flow-cytometric data will be acquired with a 10-color BD FACSCanto™ II Flow Cytometer and FACSDiva 8.0.2 software (BD Bioscience, USA). FSC files will be analyzed using FlowJo v10.8 1 (BD Biosciences, USA).

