### 1.1. Immunotherapy with Immune Checkpoint Inhibitors in the Treatment of Malignant Melanoma

The immune system plays an important role in carcinogenesis. The suppression of immune system creates a favorable tumor microenvironment that promotes the growth and development of cancer cells. In recent years, a breakthrough in oncology has been achieved by immunotherapy with immune checkpoint inhibitors (ICIs). ICIs are monoclonal antibodies that, by binding to PD-L1/PD-1 and CTLA-4 (cytotoxic T-lymphocyte-associated protein 4), enable immune cells to act against tumors [10]. *PD-1* is a transmembrane receptor on various cells of the immune system (T and B lymphocytes, macrophages, natural killer cells and dendritic cells). Transmembrane glycoprotein *PD-L1* is found on immune cells, such as macrophages, some activated T and B lymphocytes, dendritic and epithelial cells, and is also present on tumor cells, where it enables so-called “immune escape”. The binding of PD-1 to PD-L1 initiates a negative regulatory loop of T lymphocytes and other immune cells, thereby enabling the proliferation of cancer cells. According to recent research, PD-L1 can also independently activate proliferative tumor pathways (PI3K/AKT, MAPK, JAK/STAT, Hedgehog and others) [11]. CTLA-4 appears as a protein receptor in regulatory T lymphocytes and, by binding to the B7 protein on antigen-presenting cells, initiates the inhibition of the immune response [5].

Immunotherapy with PD-1/PD-L1 and CTLA-4 inhibitors in the treatment of patients with metastatic malignant melanoma has greatly improved prognosis and survival. Life expectancy has increased from less than 12 months to more than 40 months. Immunotherapeutics from the group of PD-1 inhibitors (nivolumab, pembrolizumab), a combination of two-tier immunotherapy of PD-1 and CTLA-4 inhibitors (nivolumab and ipilimumab) and BRAF inhibitors (vemurafenib, dabrafenib)—and MEK (cobimetinib, trametinib) signaling pathways in the case of BRAF V600 mutation—are used as the first line treatment for metastatic melanoma according to ASCO and NCCN guidelines [12].

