## 2. Methods and Design

### 2.1. Study Design

The study is cohort-prospective, non-randomized and non-interventional (Figure 1). It will assess the association between the predominant composition of the human gut microbiome and the response to immunotherapy treatment with PD-1 and CTLA-4 inhibitors in metastatic malignant melanoma. It will also observe whether specific biomarkers (host immune cells population, PD-L1 and IFNγ expression) correlate with the predominant composition of the gut microbiome and the response to treatment with immunotherapy.

Patients with metastatic malignant melanoma who will be treated with immunotherapy in the first line in the three-year period from October 2022 to October 2025 will be included in the research. One-hundred-and-fifty patients will be included. Consenting patients will be asked to provide clinical data and donate biological samples before, during and after completing their treatment. Patient data will be anonymized—date of birth, gender, date of diagnosis, performance status at initiation of treatment, liver enzymes, tumor markers—LDH, S100, localization, BRAF status, treatment type, response to immunotherapy, treatment time, immune-related adverse events of treatment.

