#### 2.3.6. Assessments during the Study

Patients will be followed up at their routine visits at the clinic. The follow-up will be scheduled at 3- or 4-week intervals, depending on the ICIs treatment regimen, when routine examination and laboratory test will be taken. Study-specific data will be collected at three different time points: up to 4 weeks before the start of treatment, at the 12th (+/−2 weeks) and 28th week (+/−2 weeks). Study-specific data will be taken additionally, if suspected disease progression and the appearance of immune-related adverse events or if indicated by the oncologist (Table 1).

Patients will be followed up regularly for the time of the treatment for the first 12 months. The study will be prematurely terminated in an event occurrence defined as disease progression/hyperprogression; by the physician’s choice in severe immune-related adverse events; when high doses of systemic corticosteroid (dexamethasone 4 mg/day or equivalent or higher) or prolonged antibiotic treatment are present; or by the patient’s choice. Before each stool sample donation, the patient will fulfill a questionnaire regarding eating habits, alcohol and tobacco consumption and medications. In the case of antibiotic treatment, the stool sample will be donated after 3 weeks of the last antibiotic dose taken.

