#### 2.5.4. Statistical Methods

The gastrointestinal microbiome, PD-L1 and Interferon Gamma expression will be correlated with one year of PFS as the primary outcome of the study. An interim analysis will be made after the first 20 included patients.

We will analyze the 16S rRNA sequences with the appropriate software tools from the Mothur software package, and we will perform analysis of molecular variance (AMOVA) and principal coordinate analysis (PCoA). For the statistical analysis of the differences in the representation of the sequences of individual bacterial groups in the studied microbiomes, we will use the DeSeq 2 package from the R programming environment. The association between phylogenetic diversity, taxonomic units, immune cells and the objective response to treatment will be determined using the Wilcoxon test. To compare values at different time points, we will use the paired *t*-test or corresponding non-parametric alternative. When comparing several groups at the same time, we will use the Kruskal–Wallis test. All differences will be considered statistically significant when *p* < 0.05.

The Kaplan–Meier method will be used to calculate survival (PFS), and the survival comparison of multiple groups will be calculated using the log-rank test. The association between the change in PD-L1 or IFNγ expression and response to treatment will be assessed using a logistic regression model and a multivariate model in which different variables will be included. Pearson’s or Spearman’s correlation test will be used to correlate changes in PD-L1 or IFNγ expression levels in tumor and blood.

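### The OS analysis in 2.5.2 has an unfilled follow-up length, and the only follow-up with a stated duration stops at progression or within 12 months

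*Protocol article*

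**What the plan says.** Within the flow-cytometry description, section 2.5.2 commits to a survival analysis: "The correlation of the analyzed immune cells and their subsets with patient PFS and OS will be also calculated". The next sentence should give its horizon but reads "Survival analysis will be based on an X-year patient follow-up". The sentence is otherwise intact and carries no redaction mark, and no other section supplies the number.

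Section 2.3.6 gives the only follow-up with a stated length: "Patients will be followed up regularly for the time of the treatment for the first 12 months". It then lists what ends participation early, beginning "The study will be prematurely terminated in an event occurrence defined as disease progression/hyperprogression". The other reasons are severe immune-related adverse events at the physician's choice, high-dose systemic corticosteroids, prolonged antibiotics, and the patient's choice.

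Three other places bear on this:

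- Section 2.5.4 says that the biomarkers "will be correlated with one year of PFS as the primary outcome of the study". It names Kaplan–Meier and log-rank for PFS and does not mention OS.
- Section 2.1 says "One-hundred-and-fifty patients will be included" and sets a three-year enrolment window. It also expects clinical data and samples after treatment is completed, but gives no duration. Its list of data items has neither vital status nor date of death.
- Section 1.1 describes the outlook under immunotherapy: "Life expectancy has increased from less than 12 months to more than 40 months".

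**The concern.** An OS analysis needs a defined horizon and a way of learning about deaths up to that horizon. For this one the horizon is blank, and the only follow-up with a stated duration does not supply the deaths.

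Two things are at stake. First, in metastatic melanoma most deaths come after progression. If observation stops at progression, those deaths are either never seen or the patients are censored just as their risk of death rises. That is informative censoring, which Kaplan–Meier and log-rank methods do not correct. The same applies, less predictably, to patients who leave for toxicity, corticosteroids or antibiotics, since each of these may be related to prognosis and to the immune-cell measurements.

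Second, a blank horizon can be filled after results are seen. Section 2.5.2 examines T cells, CD4+ and CD8+ subsets, macrophages and their M1-like and M2-like subsets, with PD-1 and PD-L1 on each, and 2.5.4 treats any p below 0.05 as significant. A free choice of follow-up length adds to the room for a selected biomarker–OS association.

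**Working it through.** The article gives no event count, power or follow-up figure for OS, so there is no stated figure to reproduce. The check has two parts.

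**What the follow-up captures.** Setting 2.5.2 beside 2.3.6:

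- If X is 1, the length agrees with the 12 months in 2.3.6, but deaths after progression or after leaving treatment still fall outside the follow-up described there.
- If X is 2 or 3, that gap remains, and follow-up beyond 12 months is also not described.

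So for any X of 1 or more, 2.3.6 does not provide the data that the OS analysis needs.

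**How many deaths to expect.** Inputs: N = 150 and a 36-month enrolment window (2.1); 12 months of follow-up (2.3.6); survival of more than 40 months (1.1). Assumptions: survival is exponential, 40 months is read as a median, and medians of 24 and 60 months are taken as a range.

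Hazard: λ = ln 2 / median. At 40 months, λ = 0.6931/40 = 0.01733 per month.

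(a) Complete 12-month follow-up, with no early exit:

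deaths = 150 × (1 − exp(−12λ)) = 150 × (1 − exp(−0.208)) = 150 × 0.188 = 28.2

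(b) Common cut-off 12 months after last enrolment, with uniform accrual over 36 months, so that follow-up is uniform on 12 to 48 months:

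deaths = 150 × [1 − (exp(−12λ) − exp(−48λ)) / (36λ)]
= 150 × [1 − (0.8123 − 0.4353)/0.6238] = 150 × 0.396 = 59.4

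| Assumed median OS | (a) complete 12 months | (b) common cut-off |
|---|---|---|
| 24 months | 43.9 | 84.0 |
| 40 months | 28.2 | 59.4 |
| 60 months | 19.4 | 43.2 |

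For 24 months under (b): λ = 0.02888, and 150 × [1 − (0.7071 − 0.2500)/1.0397] = 84.0.

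For comparison, following everyone for exactly 2 or 3 years at a 40-month median gives 51 and 70 deaths.

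**What those counts support.** Schoenfeld approximation, two-sided 0.05 (the article does not state sidedness), biomarker split at the median:

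- The smallest hazard ratio detectable with 80% power is exp(−(1.960 + 0.842)/√(d/4)). With d = 28 this is 0.35; with d = 59 it is 0.48.
- Power for a hazard ratio of 0.5 is about 45% with 28 deaths and about 76% with 59.
- 80% power for a hazard ratio of 0.5 needs 66 deaths.

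Column (a) is not the count under the text as written, because 2.3.6 ends participation at progression and other events. The article gives no PFS or discontinuation rates from which to compute that loss. For each assumed median, (a) is an upper figure for what 12-month follow-up would capture.

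**The case against.** The strongest reply is that one unfilled number in a peripheral analysis is being made to carry too much. Several parts of it stand.

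- An unknown X does not in itself contradict 12 months. X = 1 would match both 2.3.6 and the one-year primary outcome. A reader might infer that the two sections conflict outright, or that OS will necessarily be read from about 28 early deaths. The text supports neither: the horizon is undefined, and 28 is what one reading of it would give.
- A reader might also infer that survival analysis as a whole lacks a horizon. It does not, since 2.5.4 fixes one-year PFS. OS is in none of the primary, secondary or exploratory objectives (2.2) and rests on one sentence in 2.5.2.
- It would go too far to say that later deaths are discarded. Section 2.3.6 is silent on vital status, 2.1 mentions data after treatment, and a fuller protocol may say more.
- The 40-month figure is given as life expectancy, not as a median. The cohort admits performance status 0–2, and the introduction cites response in at most half of patients and hyperprogression in up to 30%. A constant hazard is therefore doubtful, and early deaths may be more frequent. That is why the 24-month row is shown.
- The cut-off used in (b) is one reasonable choice that the article does not dictate. At a 40-month median its 59 deaths still fall short of 66.

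What does not stand is the argument that this is mere detail left to a fuller document. The article includes the sentence that should state the follow-up and leaves the value blank, and the follow-up it does define stops before most deaths would occur.

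**Conclusion.** The concern holds, for the immune-cell OS analysis only. Its follow-up length is an unfilled placeholder, and the only follow-up with a stated duration covers time on treatment within 12 months and ends at progression, among other events. Followed as written, post-progression and post-exit deaths would be missed or informatively censored, and the horizon is open to choice after the data are seen. This part needs no numerical assumption.

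The size does rest on assumptions. At an exponential 40-month median, complete 12-month follow-up yields about 28 deaths among 150 patients, with a range of about 19 to 44 for medians of 60 to 24 months. A common cut-off 12 months after last enrolment roughly doubles each figure. The primary one-year PFS outcome and the listed objectives are unaffected, so this should be corrected but does not threaten the main study.

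**What to change.** In 2.5.2, replace the placeholder with a pre-specified OS rule, for example from first ICI dose to a common cut-off date such as 12 months after the last patient is enrolled. The exact cut-off is the sponsor's choice; it must be fixed before outcome data are examined.

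In 2.3.6, state that vital status is collected for all enrolled patients regardless of progression, end of treatment or end of sampling, with censoring at the date last known alive. This changes data collection only and leaves treatment and sampling rules alone. In 2.1, add vital status and date of death to the listed data items.

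If vital status will not be collected in this way, delete OS from 2.5.2.

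The cost is a few sentences and one record look-up per patient at the cut-off. The OS result arrives later, and the consent must cover the look-up. That routine records can supply vital status is an assumption for the sponsor to confirm.
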